### Data collection and management

3.11

Table 3 shows the schedule of evaluations. Data of each participant were collected on case report forms (CRFs) and then electronically recorded on a computer. CRF1 records participants' baseline information and it was filled in when neonates were included in the trial. CFR2, which includes information about the outcome of this trial, will be filled in during the trial and when neonates discharge with advice.

**TABLE 3 nop21733-tbl-0003:** Schedule of evaluations.

	Staff member	CRF	T1	T2	T3	T4	T5	T6
Symptom of FI	Neonatal assistant	CRF1	**×**					
Informed consent	Research assistant	CRF1	**×**					
Contact information	Research assistant	CRF1	**×**					
Sex	Neonatal physician	CRF1		**×**				
Gestational age	Neonatal physician	CRF1		**×**	**×**			
Mode of delivery	Neonatal physician	CRF1		**×**				
Apgar score	Neonatal physician	CRF1		**×**				
Maternal issues	Neonatal physician	CRF1		**×**				
Weight	Neonatal nurse	CRF2		**×**	**×**			**×**
Gastric residual volume	Neonatal nurse	CRF2				**×**	**×**	
Abdominal circumference	Neonatal nurse	CRF2				**×**	**×**	
Frequency of defecation	Neonatal physician	CRF2				**×**	**×**	
Length	Neonatal nurse	CRF2		**×**				**×**
Head circumference	Neonatal nurse	CRF2		**×**				**×**
Time to achieving total enteral nutrition	Neonatal physician	CRF2						**×**
Duration of abdominal distension	Neonatal physician	CRF2						**×**
Duration of vomiting	Neonatal physician	CRF2						**×**

*Note*: T1, screening; T2, baseline evaluation; T3 randomization; T4, day 1 of intervention; T5, day 7 of intervention; T6, discharge.

Once recorded, data are locked to prevent changes. Access to the data is limited to researchers directly involved with this trial. Data about participants who discontinue or deviate from intervention will not be included in statistical analysis.

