### Participants: Inclusion/exclusion criteria

3.3

Table 1 specifies the criteria for inclusion, exclusion, termination and exit criteria. Inclusion and exclusion criteria were defined according to previous literature (Baldassarre et al., 2019; Ng et al., 2018; Yakobson et al., 2020).

**TABLE 1 nop21733-tbl-0001:** Inclusion, exclusion, termination and exit criteria.

*Inclusion criteria*
Meet the FI diagnostic criteria
Admitted to the Neonatal Treatment Center of the Affiliated Children's Hospital of Chongqing Medical University within 24 h after birth
28 weeks ≤ gestational age ≤ 34 weeks, 1000 g ≤ birth weight ≤ 2000 g
In clinically stable condition
The neonate's guardians are willing to participate in this trial
*Exclusion criteria*
Apgar score less than 4 at 5 min
Neonates with skin disease, intestinal obstruction, sepsis, necrotizing enterocolitis, gastrointestinal malformation, congenital heart disease, central nervous system disorder, immune deficiency, or any other disease that may affect the ability to eat and normal growth before recruitment
Neonates who need surgery which requires general anaesthesia (except for ligation of patent ductus arteriosus) before the day of randomization
Neonates whose blood pressure is not stable (using dopamine <5 mg /kg/min is permitted)
Ventilator dependent or FiO_2_ (Fraction of inspired oxygen) > 40% on the day of randomization (continuous positive airway pressure, nasal intubation, oxygen mask are allowed)
Neonates who are diagnosed with Grade III or IV ventricular haemorrhage (IVH) on the day or before randomization
*Termination criteria*
Discharge in a stable condition with doctor's advice
*Exit criteria*
Death or discharge before achieving total enteral nutrition
Guardian request to withdraw from the trail

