### Intervention

3.8

Intervention was provided by a massager (who has rich experience of neonatal nursing and has qualifications for neonatal massage). A 15‐min massage was performed on the massage group twice a day for 7 days. The massage began 30 min before feeding. Before the massage, the massager would thoroughly wash and disinfect hands and warm them. Neonates were placed in the supine position, and their heads and shoulders were pad 30°–45°. All the neonates were under ECG monitoring during massage.

The method of massage, frequency and application time were decided according to expert opinions found in previous studies (Diego et al., 2007; Heinonen et al., 2016; Kim & Bang, 2018; Tekgündüz et al., 2014; Zhu & Gong, 2021). And its biological plausibility and safety have been validated. Massage includes two parts: abdominal massage and skin stroking.

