### Safety

3.9

As safety of massage has been proven in previous studies, our intervention would not induce any complications in most cases. And we took several measurements to avoid the occurrence of adverse events. The strength of massage was controlled so that the baby's skin changes just from pink to white. During massage, the massager paid close attention to the ECG monitor. Massage was suspended when the baby's vital signs (such as respiratory rate, heart rate and oxygen saturation) were not stable (Diego et al., 2009; Indrio et al., 2011), or the baby began to cry, urinate or defecate. Massager would continue massage only when the baby returns to a stable condition.

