#### Primary outcome

3.10.1

The time (day) from initiation of enteral nutrition to total enteral nutrition, which is defined as a daily intake of ≥120 mL/Kg/day (Abdallah et al., 2013).

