### Statistical analysis

3.12

After the data for the entire sample has been collected, it will be performed using SPSS 25.0 software package. Missing data will be forecasted and filled using multiple imputations. A logistic regression model will be used to adjust for multiple potential confounders plain. Measurement data obeying the normal distribution will be expressed as mean (standard deviation), and t‐test will be used for comparing between two groups. Non‐normally distributed variables will be expressed as median (interquartile range), and compared by the use of non‐parametric Wilcoxon–Mann–Whitney test. Classification data will be described as cases count (construct Proportional) and compared using the chi‐square test or non‐parametric Wilcoxon–Mann–Whitney test. The confidence interval will be set at 95%. *p* < 0.05 will be considered statistically significant.

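### Randomised infants who discontinue or deviate from massage are dropped from the analysis, so the primary comparison is no longer the randomised one and may favour massage

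*Protocol article*

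**What the plan says.** Section 3.11 (Data collection and management) sets the analysis population in one sentence: "Data about participants who discontinue or deviate from intervention will not be included in statistical analysis". It is not limited to one endpoint, and the article does not define what counts as deviating.

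Other sections bear on how the rule would work:

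- Section 3.8 (Intervention): the massage "was performed on the massage group twice a day for 7 days". No study intervention is described for controls.
- Section 3.9 (Safety): "Massage was suspended when the baby's vital signs (such as respiratory rate, heart rate and oxygen saturation) were not stable". Crying, urinating and defecating are further triggers. The section adds: "Massager would continue massage only when the baby returns to a stable condition".
- Table 1, exit criteria: "Death or discharge before achieving total enteral nutrition" and "Guardian request to withdraw from the trail". Both can occur in either arm.
- Section 3.10.1: the primary outcome is the time "from initiation of enteral nutrition to total enteral nutrition".
- Section 3.12 (Statistical analysis): "Missing data will be forecasted and filled using multiple imputations".
- Section 3.4 (Sample size calculation): 41 per group, raised to 52 for a 20% loss rate, to detect a difference between means of 28.3 and 33.5 days.

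**The concern.** Randomisation makes the two groups comparable at the moment of allocation. Removing infants for what happens afterwards gives that up. Here the removal is also likely to be unequal, because an infant in the control group has no massage to stop or deviate from.

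If the infants who stop massage tend to be those with a slower course, the infants left in the massage arm look better than the arm as randomised, while their counterparts stay in the control arm. A difference could then appear without any effect of massage. Infants who tolerate massage poorly would also be missing from the result, although the stated aim includes showing that the method is safe. Because deviation is undefined, the number removed is open to judgement after the event.

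**Working it through.** **1. The plan's own figure.** 41 / (1 − 0.20) = 51.25, rounded up to 52 per group and 104 in total. The loss step reproduces. It restores the number analysed, but does nothing about who is removed.

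**2. Standard deviation (assumption).** Section 3.4 gives none. Solving n = 2(SD × Zsum / δ)² for SD, with n = 41 and δ = 33.5 − 28.3 = 5.2 days, gives SD = 5.2 × √20.5 / Zsum.

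- Stated α 0.025 (taken as one-sided) and power 0.90: Zsum = 1.960 + 1.282 = 3.242, SD = 7.26 days.
- Printed Z values: Zsum = 1.64 + 0.84 = 2.48, SD = 9.49 days.

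The two sets of inputs disagree, so both SDs are carried forward as a range.

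**3. Expected shift.** Suppose a fraction f of the massage arm is removed, being those highest on a severity score that correlates ρ with time to full feeds. The mean of those who remain falls by about ρ × SD × φ(z) / (1 − f), where φ is the normal density and z the upper-f normal quantile. For 10 of 52 infants removed, φ(z)/(1 − f) = 0.338. At ρ = 0.5 the shift is 0.5 × 7.26 × 0.338 = 1.23 days, or 0.5 × 9.49 × 0.338 = 1.60 days.

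**4. Simulation.** No true effect, 52 per arm, normal outcomes, two-sided t-test at 0.05, at least 20,000 replicates. Here 10% means 5 infants and 20% means 10.

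| Massage excluded | Control excluded | ρ | Spurious benefit, days (SD 7.26 to 9.49) | Type I error |
|---|---|---|---|---|
| 10% or 20% | 0 | 0 | 0 | 0.05 |
| 10% | 0 | 0.3 | 0.4 to 0.5 | 0.06 |
| 10% | 0 | 0.5 | 0.7 to 0.9 | 0.08 |
| 20% | 0 | 0.5 | 1.2 to 1.6 | 0.13 |
| 20% | 10% | 0.5 | 0.5 to 0.7 | 0.07 to 0.08 |

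The fourth row agrees with the formula in step 3. Relative to the planned effect it is 1.2/5.2 = 23% to 1.6/5.2 = 31%.

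**5. Effect of the fix on power.** With all 52 per arm analysed and the effect undiluted, power at one-sided 0.025 is about 0.95 at SD 7.26 (0.90 with 41 per arm), or about 0.80 at SD 9.49 (0.70 with 41 per arm).

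**The case against.** Four points can be made for the plan, and each limits the claim.

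- **Severity is not documented.** A reader might infer that the rule removes mostly sicker massage infants. The article does not show this. Section 3.9 describes a temporary pause, which also follows crying, urinating or defecating, and massage then resumes. Pausing and resuming in that way follows the protocol, so it is not obviously a deviation. Infants must also be clinically stable at entry. A link with severity is plausible, no more.
- **The exclusion need not be wholly one-sided.** Death, discharge before full feeds and guardian withdrawal can occur in both arms, and the article does not say whether they count as discontinuing. The last row of the table shows that some control exclusions reduce the bias.
- **The size rests on assumptions.** The 20% in section 3.4 is an all-cause allowance for each group, not a forecast of massage-arm exclusions. The correlations are assumed, and the SD is back-solved.
- **Multiple imputation is not contradicted.** A reader might see a conflict between sections 3.11 and 3.12. There is none in the strict sense: missing values can be imputed among the infants who are retained. The imputation sentence simply does not bring the excluded infants back.

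All four stand, but none rescues the rule. An analysis plan that is not shown may add detail, but this is not a detail left open: the article states an exclusion, without qualification and with no as-randomised analysis beside it.

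**Conclusion.** The rule is wrong as written for a randomised superiority trial. It selects infants on events after randomisation, and by design it can act mainly on the massage arm. This conclusion needs no assumption about severity.

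The direction and size of the bias are conditional. Bias towards massage arises if the excluded infants are slower feeders. In the scenarios tabulated, with no true effect, it runs from none to about 1.6 days, with type I error from 0.05 to 0.13. Confidence in the defect is high; confidence in how large it will prove is moderate at best, because the documents give no SD, no definition of deviation and no expected count.

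**What to change.** Replace the sentence in section 3.11 with: *All randomised infants are analysed in the group to which they were randomised, whatever massage they received, with outcome collection continued to discharge unless the guardian withdraws consent for data use; excluding infants who discontinue or deviate is a per-protocol sensitivity analysis only.*

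Keep multiple imputation for values that are missing. State separately how infants who die or are discharged before full enteral nutrition enter the primary analysis, since they have no observed primary outcome and the as-randomised sentence alone does not settle this. Define deviation for the sensitivity analysis.

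Cost: a wording change. The total stays at 104, and Table 3 already schedules outcome recording at discharge, so no visit is added. The effect estimate may be slightly diluted by infants who received less massage. Recruitment began in April 2021, so outcome data may be incomplete for any infant who has already left; those cases should be listed by arm with the reason.

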## BACKGROUND

1

Over 14.9 million babies are born prematurely across the world every year, and the number is still increasing (Heinonen et al., 2016). Due to immature gastrointestinal function, premature newborns especially those born before 34 weeks, are susceptible to feeding intolerance (FI) (Asadi et al., 2019), and its morbidity could achieve 70% (Ng et al., 2019). Currently, there is no universal definition of FI, the widely accepted one is the following: the gastric residual volume (GRV) was 50% greater than the last feeding volume, with abdominal distension or vomiting (Moore & Wilson, 2011).

FI could badly influence newborns' health. During the neonatal period, it may lead to malnutrition, delayed enteral nutrition, prolonged hospitalization, growth restriction and increase the risk of sepsis and serious gastrointestinal complications such as necrotizing enterocolitis (NEC) (Meister et al., 2019; Neu, 2007). Additionally, it may lead to long‐term negative outcomes such as visceral obesity, glucose intolerance, and increased risk of cardiovascular disease, negative neurodevelopmental outcomes in adulthood (Asadi et al., 2019). At present, treatment for FI includes breastfeeding, modifications in feeding regimes, use of probiotics or medicine, but effectiveness and safety of these methods remain controversial (Basu & Smith, 2020; Fanaro, 2012; Sukwuttichai et al., 2021), feeding intolerance (FI) is still a thorny issue affecting the prognosis of preterm infants. So it is important to find an effective way to cure FI, contributing to recovery of gastrointestinal function and improving long‐term health of preterm infants.

In recent years, massage therapy has been frequently used in neonatal wards for the prevention of FI. Studies have shown that massage could prevent gastric retention and abdominal distention in premature infants, and reduce the length of stay. In addition, massage could stimulate the digestive system and the vagus nerve in premature infants, potentially improving their physical growth (Diego et al., 2007; Heinonen et al., 2016; Tekgündüz et al., 2014). However, there is no consensus on the efficacy of massage in the treatment of FI.

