### Sample size calculation

3.4

We estimated the sample size by the use of PASS 15. According to a previous study (Kim & Bang, 2018), the average time of achieving total enteral nutrition in the intervention group and control group is 28.3 days and 33.5 days respectively. This study is a superiority test of two independent means, desired power was set at 0.9, *α* was set at 0.025, *Zα* = 1.64, *Zβ* = 0.84. *σ* represents the standard deviation, and δ represents the difference between the mean values of each group. After calculation, 41 participants were needed for each group. Considering a 20% loss rate, 52 participants were needed for each group. A total of 104 participants should be included.

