### Validity and reliability

3.13

An impartial scientific and administrative Steering Committee will monitor the whole course of the study, the evaluation of new information, patient safety, and protocol adherence. Cronbach's alpha is used to calculate reliability. Cronbach's alpha will be calculated for each dimension to assess the consistency of researchers evaluating neonates' condition. Cronbach's alpha between 0.7 and 0.8 is regarded as acceptable and 0.8 or higher is optimal (Cronbach, 1951).

Data monitoring committee (DMC) is responsible for making sure that researcher performs the recruitment, clinicians document data of participants and trial statisticians are blinded to the allocation group until the results are finalized. The DMC also discusses interim analyses and considers protocol modifications during the study period.

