### Current study status

3.14

The experiment is still ongoing at the time of submission of this paper; however, subject recruitment began in April 2021. Currently, the study has not completed the recruiting phase, and it is anticipated that the experiment will complete in December 2023.

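### The stated analysis set drops infants who stop or depart from the intervention, mainly in the massage arm, so the primary comparison is not between the randomized groups

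*Protocol article*

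**What the plan says.** Three parts of the protocol article bear on who is analysed.

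- **Data collection and management (3.11)** sets the rule: "Data about participants who discontinue or deviate from intervention will not be included in statistical analysis". It has no qualification and is not limited to a secondary analysis. Neither discontinuing nor deviating is defined.
- **Statistical analysis (3.12)** names no analysis set. On incomplete data it says: "Missing data will be forecasted and filled using multiple imputations".
- **Table 1 (3.3)** lists exit criteria that apply to both arms: "Death or discharge before achieving total enteral nutrition", and withdrawal at the guardian's request.

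Two further sections show where the rule will act. Intervention (3.8) gives the massage arm two 15-minute sessions daily for a week, 14 in all, and describes no scheduled procedure for controls. Safety (3.9) suspends a session for unstable vital signs, and also for crying, urination or defecation. On resuming, it says: "Massager would continue massage only when the baby returns to a stable condition".

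**The concern.** The rule selects infants on something that happens after randomization and that differs by arm. A massage infant can fail to complete the course, whereas a control has almost nothing to discontinue. A control could still deviate, for instance by receiving massage, so the exclusions are mainly, not only, in the massage arm.

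The primary outcome is days from the start of enteral feeding to full enteral nutrition. Instability is one stated reason for suspending massage, and unstable infants may well feed slowly. If such infants leave the massage arm while similar controls stay, the massage mean shortens even when massage does nothing. Whatever the direction, the two analysed groups are no longer the two randomized groups, and that comparability is the main protection a trial of 104 infants has.

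Multiple imputation does not repair this. It fills values that are missing, whereas this rule discards infants whose outcome may have been recorded. The loss allowance in the sample size section protects the number of infants, not the balance between arms.

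**Working it through.** **Inputs from the document (Sample size calculation, 3.4).** Assumed means 28.3 and 33.5 days; 41 per group before loss; 20% loss; 52 per group; power 0.9; alpha 0.025; printed Z values 1.64 and 0.84. No value is given for the standard deviation (SD), and no discontinuation rate is given anywhere.

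**Step 1. Reproduce the plan's figure.** The plan says: "Considering a 20% loss rate, 52 participants were needed for each group". 41 / (1 − 0.20) = 51.25, rounded up to 52 per group and 104 in total. This agrees. The allowance is 0.20 × 52 = 10.4 infants per arm; the plan does not say how many would be massage discontinuations.

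**Step 2. Planned difference.** 33.5 − 28.3 = 5.2 days.

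**Step 3. SD implied by 41 per group, for scale.** SD = √[41 × 5.2² / (2(Zα + Zβ)²)].

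- Printed Z values: √[1108.64 / (2 × 2.48²)] = 9.49 days.
- One-sided alpha 0.025 and power 0.9 (Z 1.96 and 1.2816): √[1108.64 / (2 × 3.2416²)] = 7.26 days.

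**Step 4. Shift from dropping infants in one arm.** Let k of 52 infants lie on average D days above the full-arm mean m. The remaining mean is [52m − k(m + D)] / (52 − k) = m − kD / (52 − k), so the arm mean falls by kD / (52 − k). Both k and D are assumptions. D = 7 days is 0.74 to 0.96 SD; D = 21 days is 2.21 to 2.89 SD.

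| Dropped (k) | D = 0 | D = 7 days | D = 21 days |
|---|---|---|---|
| 1 | 0 | 7/51 = 0.14 d (2.6% of 5.2) | 21/51 = 0.41 d (7.9%) |
| 3 | 0 | 21/49 = 0.43 d (8.2%) | 63/49 = 1.29 d (24.7%) |

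**Step 5. Feasibility of larger values.** For k = 5 and D = 21 the formula gives 105/47 = 2.23 days, or 43% of 5.2. The split between dropped and retained infants would then contribute (5 × 21² + 47 × 2.23²) / 52 = 46.9 days² to the arm's variance. That is about 89% of 7.26² = 52.7 and about 52% of 9.49² = 90. The first leaves almost no room for ordinary variation between infants, so this case is set aside. For k = 3 and D = 21 the contribution is (3 × 21² + 49 × 1.29²) / 52 = 27.0 days², about 51% and 30%. That is extreme but possible.

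**Step 6. Effect on the type I error.** Suppose there is no true effect, a share f of the massage arm is dropped, and the dropped infants are c SDs slower than the arm mean. The shift is f·c·SD / (1 − f) and its standard error is SD·√[1/52 + 1/(52(1 − f))]. The SD cancels in the ratio. At two-sided 0.05, by normal approximation:

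| f | c | Shift (SD 7.2 to 9.4) | Type I error |
|---|---|---|---|
| any | 0 | 0 | 5% |
| 5% | 0.5 | about 0.2 d | 5.2% |
| 10% | 0.5 | 0.4 to 0.5 d | 5.9% |
| 10% | 1 | 0.8 to 1.0 d | 8.6% |

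**The case against.** The strongest reply accepts the rule as written but disputes that it does much harm, and most of this reply stands.

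- **Direction is not established.** Safety (3.9) describes only suspending and resuming, and three of its triggers (crying, urination, defecation) say nothing about slow feeding. With the terms undefined, it is not known whether one suspended session leads to exclusion. If the dropped infants resemble the rest, there is no bias.
- **The vulnerable group is narrow.** Table 1 admits only clinically stable infants and excludes prior sepsis, necrotizing enterocolitis (NEC) and obstruction. Massage lasts 7 days, against assumed times to full feeds of about a month. Some of the sickest infants leave through exit criteria that treat both arms alike.
- **The size may be small.** One dropped infant moves the arm mean by at most 8% of the planned difference under the assumptions above.

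A reader might infer a stronger claim: that infants who develop NEC or sepsis will be taken off massage and out of the analysis, so that the result is bound to favour massage. The Background links feeding intolerance to those illnesses, but no section says that massage is permanently stopped for them or how often that would happen.

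An analysis plan that is not shown might define an as-randomized set. It would then contradict the published rule, which would still need correcting. None of these replies removes the central point: the only analysis described selects on adherence after randomization, in a way that differs by arm.

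**Conclusion.** The point holds as a defect of the stated analysis set and should be fixed. That the exclusions fall mainly on the massage arm follows from the Intervention and Safety sections. A tilt towards massage is plausible but remains an inference, because it requires the dropped infants to be slower to full feeds.

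The size is unknown. Under the assumptions of 1 to 3 exclusions from 52 and an excess of 7 to 21 days, the shift is about 0.1 to 1.3 days, or roughly 3% to 25% of the planned 5.2 days. It is nil if the excluded infants are typical.

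Two larger figures should not be relied on. The 43% case needs a spread that the implied SD barely allows. A type I error of 22.5% arises with f = 20% and c = 1, but that requires the whole loss allowance to be massage-arm exclusions averaging one SD slower, and nothing in the article says so.

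**What to change.** Replace the exclusion sentence in section 3.11 along these lines: *The primary analysis includes all randomized infants in the group to which they were assigned, whatever massage they received. An analysis restricted to infants who adhered to the intervention is secondary.*

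State in the same place how the Table 1 exits are treated, since otherwise the as-randomized set would be incomplete. Infants who die, are discharged before full feeds, or are withdrawn by a guardian stay in the set, with their data up to exit used. The unobserved primary outcome is handled by the same rule in both arms. For example, the multiple imputation already planned could cover early discharge and withdrawal, with deaths reported separately by arm and covered in a sensitivity analysis. Any infants already set aside under the present rule should be restored.

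**Cost.** The change is to the text only. The target stays at 52 per group, and Table 3 already records time to full enteral nutrition at discharge, so no visit is added. The article reports, "Currently, the study has not completed the recruiting phase", so at submission the rule could still be changed for every infant. The ethics committee and the registry must be told, as the ethics section provides. The downside is that some massage-arm infants will be analysed with less than a full week of massage, which may dilute the estimated effect. The adherent-only analysis can be reported beside it, labelled as secondary.
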